## Abstract

**Background:**

Fetal alcohol spectrum disorder (FASD) is one of the most common causes of preventable intellectual disability, and the key associated deficits are in executive function (EF). Aspects of EF can be improved using cognitive training interventions. The highest prevalence of FASD globally (at a rate of 135.1 per 1000) has been found in a South African population in the Western Cape province. There is a shortage of specialized health service personnel, and there are limited remedial services. Computer-based cognitive training, if age and culturally appropriate, could be an effective way to provide the interventions with minimal need for skilled personnel and other resources. The Foundation for Alcohol Related Research has developed such a program for the South African context.

**Objective:**

This protocol aimed to evaluate whether it is feasible to use computerized cognitive training in a resource-poor context to improve cognitive function in children exposed to alcohol in utero.

**Methods:**

We are conducting a randomized controlled trial in the Saldanha Bay Municipal area, evaluating a custom-developed cognitive training program to improve the cognitive function of children aged between 4 and 6 years who were exposed to alcohol in the prenatal stage. Participants will be recruited from local Early Childhood Development centers. Community workers will interview biological mothers to identify alcohol-exposed pregnancies. Alcohol-exposed children will be randomized into an intervention or a control group of 40 participants each using block randomization. A group of 40 children not exposed to alcohol will be included in a normative group using individual randomization. The intervention group will play the game for 6 months (40 sessions). Normative and control groups will receive no intervention. Neurodevelopmental assessments will be done at baseline and upon completion of the study with all participants.

**Results:**

The intervention has started, and all baseline assessments have been done at the time of submission.

**Conclusions:**

This study will provide insight into whether computerized cognitive training is viable and effective in the South African context. It has the potential to provide a means of intervention globally and in other resource-poor context and expand the knowledge base regarding executive functioning and FASD. This paper presents the research protocol and intervention design of the study.

**Trial Registration:**

ISRCTN Registry ISRCTN17244156; http://www.isrctn.com/ISRCTN17244156.

**International Registered Report Identifier (IRRID):**

DERR1-10.2196/14489

## Introduction

### Background

Consuming alcohol during pregnancy is one of the most common causes of preventable intellectual disability [1]. The teratogenic effects of alcohol can lead to a range of physical and intellectual difficulties and disabilities, grouped together under the term fetal alcohol spectrum disorders (FASDs) [2]. To date, the highest prevalence of FASD globally has been found in selected communities in South Africa, with a prevalence rate of 135.1 per 1000 in a particular population in the Western Cape province and 119.4 per 1000 in the Northern Cape provinces [3-5].

Deficits in both elementary and higher order intellectual functioning have been found in FASD. It has been established that some of the key deficits in children are in the domains of attention, information processing, and executive function (EF) [6]. The deficits found in attention are associated specifically with encoding (temporarily holding information in memory to perform mental operations on it) and shifting (flexibly moving attention between different stimulus dimensions), along with deficits in executive control [7,8]. The EF that is found to be affected includes inhibitory control, cognitive planning, and working memory [7,9].

### Cognitive Training

Dysfunctions in EF can have serious consequences and have been associated with poor school readiness, addiction, conduct disorder, and lower educational outcomes [10]. Owing to the deficits in EF, individuals with FASD struggle with integrating knowledge and basic cognitive processes required for complex tasks [7]. Intervention in these areas is crucial as deficits have an impact on social functioning, adaptive functioning, and the ability to live independently. It has been shown that aspects of EF can be improved using training and practice [11]. Interventions include physical activities such as martial arts and yoga, improved school curricula, and computerized cognitive training [11,12]. Cognitive training has shown to have an impact on task performance and on fluid intelligence (Gf) tests [13-15]. Training on specific cognitive tasks induces neuroplasticity, and although the specific mechanisms are still unclear, it is generally accepted that training impacts synaptogenesis and neurogenesis [16]. Evidence that these mechanisms can improve the brain’s functioning has been found in populations including individuals with traumatic brain injury [17], individuals with unspecified mild or moderate mental retardation [18], and children with FASD between the ages of 6 and 15 years [19].

The impact of the improvement in specific functions is not yet clear, and results of studies examining this have been mixed [14,20]. The key question in this regard is whether training can have an impact on fluid intelligence and therefore global intellectual functioning. Although the idea that training can impact Gf has been challenged [15], there is some evidence to support it [21-23]. The sequela of the cognitive deficits associated with prenatal alcohol exposure (PAE) arguably have the most severe impact on life outcomes [24,25]. Early diagnosis and intervention can improve expected life outcomes [26]. Yet, in South Africa, an acknowledged lack of specialized health services and personnel [27] means that few affected children will be diagnosed early, and those that are diagnosed will likely not have access to any remedial programs or intervention.

### Cognitive Training in Resource Poor Contexts

Cognitive training interventions do not translate easily into a resource-poor context, and even physical activities such as martial arts and yoga require a trained interventionist. Computer-based cognitive training, if age and culturally appropriate, could be an effective way to provide the interventions with minimal need for skilled personnel and other resources. Unfortunately, existing games such as cognitive carnival or Caribbean quest [19] and other brain training games require a level of computer literacy not routinely found among low-socioeconomic status (SES) children owing to low levels of exposure to computers [12]. The game, Caribbean Quest, for example, requires children to use a keyboard and mouse. These skills would have to be taught to the children, and in some settings may serve as a confounder when measuring game performance. Participants in the Caribbean Quest study also had one-on-one sessions where they were taught meta-cognitive skills. Although this proved to be effective, in a resource-poor context, this would not be viable on a large scale [19].

In comparison with the Canadian study [9], children diagnosed with FASD in South Africa live in social environments different from those in Canada and the available resources are scarce. Participants in the cited cognitive training studies were either already receiving other rehabilitation services [17,18] or the intervention went further than only providing the cognitive training game [19]. Therefore, the question remains whether computerized cognitive training can be adapted for a resource-poor context and whether it will still have an impact.

One of the main differences between the 2 contexts is the access to personal computers and laptops. To develop games for personal computers and laptops will therefore likely exclude many participants in low-SES communities. The required skills to use these devices would likely also be lacking in these communities. Moving development to mobile computing devices mitigates these complications. There may of course be a lack of familiarity with mobile devices as well, but the more intuitive touch screen interfaces will be easier to master for young children. A move to mobile computing can also benefit children in more developed countries as well, as their first exposure to technology will likely also be in the form of mobile devices or tablet computers [28]. There are of course challenges involved with mobile computing with more issues with input lag, latency, and less memory and processing power. The benefits do outweigh the complications.

Over the past 3 years, the Foundation for Alcohol Related Research (FARR) has been developing and piloting such a cognitive training program tailored to the South African context. The intervention is designed for eventual use on tablets or smartphones that are becoming more ubiquitous even in low-income communities [29]. The FARR game is focused on exercising EFs, particularly attention, inhibition, and working memory. From the outset, it was designed to be suitable for children with little to no computer literacy, to need minimum support and intervention from professionals, and have the possibility to be scaled up as an intervention.

## Methods

### Overview

We are conducting a feasibility randomized controlled trial (RCT) to evaluate the use of a custom-developed cognitive training program to improve the cognitive function of children aged between 4 and 6 years who were exposed to alcohol in the prenatal stage compared with a control group.

We hypothesize the following:

Post intervention, the intervention group will score higher on psychometric assessments of EFs than the control group.At baseline, alcohol-exposed children (both intervention and control groups) will score significantly lower on psychometric assessments of EFs compared with nonalcohol-exposed children (normative group).Post intervention, the intervention group will score higher on psychometric assessments of EFs than the control group, but lower than the normative group.Post intervention, the intervention group will show greater improvement on psychometric assessments of EFs than the control and normative groups.Improvement in game performance will be correlated with improvement on psychometric assessments of EFs.Improvement in psychometric assessments of EFs will be positively correlated with total time spent playing the game.

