### Intervention

The efficacy of cognitive training is influenced by the time spent interacting with the program and the difficulty of the tasks presented, especially in terms of whether skills that are not directly trained will improve [18]. In the first step, the specific processes to be targeted were identified using the available literature. In consultation with a software developer, the basic interface and game mechanics were designed, focusing on an intuitive interface and game mechanics that will allow the same interaction to be used with all tasks. In the alpha (initial) version, it is possible to select different tasks to ensure data can be gathered for all stages and tasks. Data that are logged will include the date and time of the play session, the response time per item, and whether the correct response was selected for each item.

The theoretical basis for the game design involves 2 different definitions of *scaffolding* in 2 different contexts. The first refers to work on childhood development and cognitive development. In this context, scaffolding refers to the support of cognitive development by reducing a complex problem to subproblems, and by solving the subproblems, the ability to solve the complex problem is gained [32]. The game was developed to incrementally increase the demands on various cognitive abilities, with continued successes on one level of difficulty eventually enabling success on a higher level of difficulty.

The second context of scaffolding refers to neuroplastic scaffolding. This term is generally used in connection with age-related cognitive decline [33], but as the target population of this intervention frequently suffers from structural brain abnormalities [2], the same concept of neuroplastic scaffolding should still apply. It refers to compensatory neural activity aimed at supporting damaged, inefficient, or poorly functioning cognitive functions. Scaffolding happens through recruitment of additional prefrontal cortex activity, neurogenesis (formation of new neuronal connections), and distributing cognitive processing over various brain structures. This theory supports the hypothesis that practice and training can enhance the process of scaffolding [34]. This was the driving principle behind the conceptualization and design of the game.

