To try and ensure long-term engagement with the game, meta-game elements have been added to the game in the form of a progress bar and animations that only appear once you have completed a set number of tasks. There will be no external rewards or incentives for playing. This is intentional as a key design consideration is that it should be fitting for context where no external rewards would be available. Tasks were designed to require effortful use of inhibitory control, cognitive planning, set shifting, and working memory for completion. The tasks have been designed in such a way that regardless of which function is being targeted, the interface and interaction with the participant does not change. If the interaction remains the same, it is easier to switch seamlessly between stages to maintain optimum difficulty.

The game we have designed (1) is easy to use regardless of computer literacy, (2) logs performance on various metrics (response times and error rates), (3) has continuously adaptive difficulty levels to maintain a suitable level of challenge, and (4) will be open access (free to distribute). Before making the intervention available, it is necessary to test whether it does in fact have an impact on cognitive development.

An alpha version of the program was piloted on a sample of normally developing children to ensure that the tasks escalate in difficulty. This provided an opportunity to ensure that the timing of visual stimuli is age appropriate for the proposed sample’s age. The pilot also provided normative data on participant performance to guide further development of the program.

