### Study Procedures

Alcohol-exposed children, as assessed by maternal interviews, will be randomized into an intervention or a control group with 40 participants in each group, using block randomization. The maternal interview will contain questions regarding alcohol use just before and during pregnancy, including the number of standard units of alcohol consumed, with 3 standard units being the threshold for determining alcohol exposure. A group of 40 unexposed children will be randomized in a group to provide normative data using individual randomization. An overview of the study design is shown in Figure 1. As the participants are drawn from a low-SES and resource-poor environment, the performance of the normative group will serve as a more suitable gauge of cognitive development in the participants’ specific contexts. This will enable us to better interpret the results of the neurodevelopmental assessments.

The SPIRIT schematic is shown in Table 1. Baseline assessments examining cognitive function will be conducted with all 3 groups. The intervention group will then play the FARR game twice a week for 6 months (40 play sessions in total). Post intervention, all 3 groups will receive follow-up cognitive assessments. Data gathered by the game will also be collected from the intervention group. All participants will start the intervention at the same level of difficulty. They will be given the opportunity to play the game during hour-long sessions facilitated by community workers. Play will, however, be self-directed; participants will be encouraged to play but will be allowed to stop at any time during a session. As participants log into the devices, they will be able to continue at the difficulty level they had previously reached.

There are 4 different stages in the game of increased complexity. After 10 trials in a stage, a participant automatically moves on to the next for 10 trials. After the fourth stage, participants start at the first stage again. The difficulty of each stage varies independently based on a participant’s performance. Getting 8 or more correct increases difficulty, getting fewer than 4 correct decreases difficulty, and otherwise the difficulty remains the same.

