#### Game Log Files

Additional data will be obtained from the log files generated by the game. The file will record error rates and response times for all tasks. Each child will be allocated a numbered tablet or a profile on a specific tablet, depending on what proves the most practical, and the log file will then be associated with their study number.

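### The play-time hypothesis rests on a raw correlation with an exposure that each child chooses, so it can show an association but not that more play causes more gain

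*Protocol article*

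**What the plan says.** The Overview lists six hypotheses, and the last reads: "Improvement in psychometric assessments of EFs will be positively correlated with total time spent playing the game". Improvement is the baseline to post-intervention difference in NEPSY-II scaled scores (Data Analysis).

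Study Procedures offers every child in the intervention group the same 40 "hour-long sessions facilitated by community workers". What each child takes up is left open: "Play will, however, be self-directed; participants will be encouraged to play but will be allowed to stop at any time during a session". The Intervention section adds: "There will be no external rewards or incentives for playing". That section also opens with a causal premise about time: "The efficacy of cognitive training is influenced by the time spent interacting with the program". On what is trained, the section Cognitive Training in Resource Poor Contexts says: "The FARR game is focused on exercising EFs, particularly attention, inhibition, and working memory".

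**The concern.** Randomisation decides who is offered the game, not how long each child plays it. Control and normative children have no play time, so this hypothesis can be examined only among the 40 treated children. There the exposure is set largely by the child's own behaviour.

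Attention is a plausible driver of how long a 4- to 6-year-old keeps playing. It is also a function that the game targets, and it may be related to how a child's test scores change over six months. A raw correlation cannot separate that route from an effect of playing.

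Because the protocol elsewhere presents time spent as something that influences efficacy, a positive result could easily be read as showing that more play produces more gain. At stake is how this one secondary result is interpreted.

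**Working it through.** The protocol gives no expected correlation, power or error rate for this hypothesis, so there is no figure to reproduce. The check asks how often a raw correlation would look positive if play time had no effect at all.

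**Inputs from the protocol**
- n = 40, the intervention group before any dropout (Study Procedures).
- Play time can range from near 0 to 40 sessions × 1 hour = 40 hours (Study Procedures).
- Significance level 0.05 (Sample Size). Sidedness is not stated. The hypothesis is directional, so both versions are shown.

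**Inputs assumed**
- One trait correlates *a* with play time and *b* with EF gain. The protocol gives neither value; 0.3 to 0.5 is shown as a range.

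**Step 1: expected correlation with no effect of play.** It is r = a × b, so 0.3 × 0.3 = 0.09, 0.4 × 0.4 = 0.16 and 0.5 × 0.5 = 0.25.

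**Step 2: correlation needed for significance.** r_crit = t / √(n − 2 + t²) with 38 degrees of freedom.
- One-sided 5%: t = 1.686, so 1.686 / √(38 + 2.843) = 0.264.
- Two-sided 5%: t = 2.024, so 2.024 / √(38 + 4.098) = 0.312. The nominal chance of a significant result in the positive direction is 2.5%.

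**Step 3: chance of exceeding it.** From 20,000 simulated samples of 40:

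| a = b | expected r | one-sided (nominal 5%) | two-sided, positive direction (nominal 2.5%) |
|---|---|---|---|
| 0.3 | 0.09 | 13.8% | 7.9% |
| 0.4 | 0.16 | 25.8% | not run |
| 0.5 | 0.25 | 47.0% | 34.3% |

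**Step 4: check by the Fisher z approximation**, with standard error 1/√37 = 0.1644.
- One-sided at r = 0.09: (0.2703 − 0.0902) / 0.1644 = 1.10, giving about 14%.
- One-sided at r = 0.25: (0.2703 − 0.2554) / 0.1644 = 0.09, giving about 46%.

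Both agree with the simulation.

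**Step 5: what adjustment could achieve.** In the two-sided simulation, partialling out the trait itself, measured without error, returned the rate to about 2.5% in every scenario. Baseline EF and age are only proxies for such a trait, so real adjustment would fall short of this.

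**Step 6: when the bias vanishes or reverses.** If a trait adds the same amount c to both assessments, the change is (Y₂ + c) − (Y₁ + c) = Y₂ − Y₁, so b = 0 and the inflation disappears. If attentive children start high and play longer, regression to the mean lowers their measured gain and pushes the correlation downwards.

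**The case against.** The strongest reply is that the hypothesis says only that two quantities are correlated. It does not call this dose-response, and the sentence about time and efficacy is background to the game's design. That is fair, and it is why the remedy is mainly one of adjustment and labelling.

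The mechanism is also narrower than it first appears. The outcome is change on age-scaled scores, so stable level differences cancel and average maturation is largely normed out. Bias needs a trait that predicts age-standardised change. The overlap between trait and outcome is partial too: in Table 2 only one of the five subtests given at all ages (Statue) falls under attention and executive function. These limits stand. They leave the possibility of confounding but not its direction or size.

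Four stronger readings are tempting, and the documents do not support them.
- A reader might infer that a positive correlation would be mostly spurious. The percentages above depend wholly on assumed values of *a* and *b*.
- A reader might infer that the decision to keep, redesign or drop the game turns on this result. The Discussion refers to the study's data in general and never mentions play time.
- A reader might count it as an error that Data Analysis describes no play-time analysis. A condensed article may leave that to the full protocol or the analysis plan.
- A reader might suppose that total time will be built by adding up response times, because Game Log Files says: "The file will record error rates and response times for all tasks". Nothing says so, and the Intervention section states that the date and time of each play session are also logged.

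**Conclusion.** The point holds in a limited form. As stated, the hypothesis is tested by an unadjusted correlation with an exposure that the child controls, so within about 40 children it is an observational comparison open to confounding.

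Under assumed trait correlations of 0.3 to 0.5 with both play time and gain, and no effect of play, a significant positive result would occur about 14% to 47% of the time (nominal 5%, one-sided) or 8% to 34% (nominal 2.5%, two-sided). With no link between the trait and change, there is no inflation. With regression to the mean, the bias could run the other way.

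The randomised comparison of intervention with control, including the primary hypothesis, is untouched. This is a cheap improvement to a secondary hypothesis, not a flaw in the trial's main result.

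**What to change.** For this hypothesis, in the intervention group:

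1. Define play time from the logged session dates and times. Regress each post-intervention NEPSY-II score analysed on play time, with the baseline score and age as covariates. Report this beside the raw correlation with the change score.
2. Report the correlation of baseline score with total play time, with sessions attended and with time per session, as a check on self-selection.
3. State in advance that the result is an exploratory association and will not be presented as evidence that more play causes more gain.

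The baseline scores, age and logs are already being collected, and nothing changes for the children. The cost is a little extra analysis and a more cautious claim. Adjusting for baseline EF and age removes only part of the confounding, and attendance is not randomised either, so the third step is needed whatever the first two show.
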